
#### PA Measures

PA will be measured with wearable activity trackers (ie, Fitbit Inspire), which will capture daily minutes of vigorous, moderate, and light exercises; sedentary time; and the number of daily steps. The data will be used to calculate weekly steps; weekly minutes of light-, moderate-, and vigorous-intensity PA; active days per week; and weekly sedentary minutes. The wearable activity trackers used in this study have demonstrated satisfactory validity on step counts measured by metabolic equivalents [27]. PA will be measured subjectively using an adapted Godin Leisure-Time Exercise Questionnaire [28,29], which asks participants to self-report their weekly minutes of strenuous, moderate, and mild or light exercise. The Godin Leisure-Time Exercise Questionnaire demonstrates good reliability and validity compared to other self-report PA measures [30,31] and has a test-retest reliability coefficient of 0.94, 0.46, and 0.48 for self-reported strenuous, moderate, and light exercises, respectively [32]. Fitbit data will serve as the primary measure of PA. Objective and subjective PA measures will be analyzed in parallel and compared. Where discrepancies arise, descriptive analyses and sensitivity tests will be conducted to explore sources of variation.

This feasibility pilot study is not powered to detect statistical significance. On the basis of prior longitudinal PA intervention studies for survivors of cancer [33-35], conservatively, we anticipate 17% total attrition. Therefore, we will enroll 72 participants to obtain a final sample of 60 (30 in each group). With 30 participants per group, we will have 80% power to detect a standardized mean difference of *d*=0.74 at 9 months, which is a large effect for a PA intervention.

#### Sedentary Behaviors

Sedentary behaviors will be measured using the Sedentary Behavior Questionnaire [36], which includes 9 common sedentary behaviors and measures the number of hours per day participants spend doing sedentary behaviors. The questionnaire has shown moderate to excellent intraclass correlation coefficients (0.48-0.93) for the time spent on each sedentary behavior and the total sedentary time and acceptable validity for measuring sitting and inactivity minutes [36].

#### Psychosocial Constructs

Psychosocial constructs will be measured using previously validated scales. PA knowledge will be measured using a behavioral capacity measure primarily developed by Short et al [37]. This measure is a 5-point Likert scale assessing participants’ knowledge about the types, intensity, frequency, and skills of doing PA [37]. Self-efficacy will be measured using a 9-item barrier self-efficacy scale and a 4-item task self-efficacy scale, which assess participants’ confidence in overcoming barriers to PA and their ability to engage in PA. The 2 self-efficacy scales have Cronbach α values of 0.96 and 0.89, respectively, among patients with cancer [38]. Outcome expectations will be measured using the 19-item Multidimensional Outcome Expectations for Exercise Scale, which has an internal consistency of 0.82, 0.84, and 0.81 for physical, self-evaluative, and social outcome expectations, respectively [39]. PA habits will be measured using a 6-point bipolar scale that assesses the 4 indicators of habit strength:: negative consequences if not done, patterned action, stimulus-response solid bonds, and automaticity [40]. The scale has Cronbach α values ranging from 0.77 to 0.85 for the 4 PA habit indicators [40]. Finally, the 4-item short version of the Physical Activity Enjoyment Scale will measure the enjoyment of doing PA [41]. This scale has internal consistency values ranging from 0.82 to 0.87 among diverse populations.

#### Patient-Reported Outcomes

Patient-reported health outcomes—commonly observed among patients with CRC and known to be positively influenced by PA—will be measured [42]. These include pain, fatigue, depression, bowel dysfunction (ie, diarrhea and constipation), quality of life, and sleep. These outcomes will be measured using the Patient-Reported Outcomes Measurement Information System (PROMIS) tools [43]. The PROMIS pain, fatigue, depression, and sleep measures have reliability coefficients of 0.96, 0.94, 0.91, and 0.88, respectively, with excellent validity among survivors of cancer [44,45]. The diarrhea and constipation scales also have internal reliability values of 0.88 and 0.89, respectively [46]. Neurotoxicity will be measured using the Functional Assessment of Cancer Therapy/Gynecologic Oncology Group–Neurotoxicity 4 scale. The internal consistency of this scale ranges from 0.73 to 0.91 at different assessment cycles among patients with cancer [47]. Quality of life will be measured using the 36-item Short Form Health Survey [48], which is a widely used survey for assessing respondents’ general physical and mental health status to determine their quality of life among survivors of CRC [49], with an acceptable to high internal consistency (>0.07) and validity observed among survivors of cancer [50,51].

#### Inflammation Biomarkers

Inflammation biomarkers that are thought to mediate the effects of PA on cancer mortality will be measured [52,53]. These include interleukin (IL)-4, IL-10, IL-6, and tumor necrosis factor α and will be measured using serum samples collected with a dried blood spot (DBS) card kit [54]. DBS cards are widely used to assess biomarkers, such as antibodies [55]. The validity of using the DBS card to measure these inflammation biomarkers in this sample will be evaluated with a comparison to whole blood samples collected using a Tasso+ kit [56]. Although DBS cards have been validated in previous studies, we will also validate them with this sample. Because the purpose of this testing is to assess the validity of DBS cards in accurately measuring the biomarkers of interest, a convenience sample is appropriate. Therefore, we will recruit the first 10 consenting participants to ensure we collect the necessary samples. Participation in this part of the study is optional and will not impact study inclusion.

### Retention

To support participants’ adherence to the study and build their understanding of the importance and value of their participation in the PACE study, we include the PACE logo (Figure 4) in all study documents to help create a sense of identity and the PACE study community. Participants will receive monthly PACE study update cards with a message thanking them for their time; a statement about what the study team hopes to learn from their participation; plans for community and scientific dissemination of findings; and a positive affirmation note from the AWF, our community partner organization described earlier. Participants will receive a US $30 gift card for completing the baseline assessment, a US $40 gift card for completing the 3-month assessment, and a US $50 gift card for completing the 9-month assessment. Intervention arm participants who complete interviews will receive an additional US $15 gift card. The 10 participants who complete the Tasso blood collections will receive an additional US $10 gift card.

**Figure 4 figure4:**
[figure not shown]
Physical Activity Centers Empowerment (PACE) logo.

### Safety and Monitoring

At weekly PACE research team meetings, all issues relevant to study progress, including but not limited to enrollment, safety, regulatory, and data collection, will be reviewed. Unanticipated adverse events will be reported to the IRB within 1 week. Study documents will be made available for inspection when requested by any of the regulatory bodies charged with the safety of human participants and the integrity of data, including, but not limited to, the Office of Human Research Ethics IRB, the Oncology Protocol Review Committee, and the North Carolina Translational and Clinical Sciences Institute Data and Safety Monitoring Board.

Potential participants’ information from RCA, including identifiable information (eg, names, phone numbers, and physical addresses), will be stored on a secure university server and will only be available to members of the research team. Identifiable information for potential participants who do not enroll in the study will be removed when the RCA recruitment is completed. For those who enroll, identifiable information will be removed at the study’s completion unless participants have agreed to be contacted by the research team for future studies.

### Statistical Data Analysis Plans

#### Reach

Descriptive statistics will be used to calculate the number of participants contacted and the percentage eligible, recruited, and retained for the duration of the study.

#### Adoption

Descriptive statistics will be used to calculate the percentage of providers who agree to have their patients contacted about the study out of the total number approached, as well as the percentage of providers who grant consent for their patients to participate in PACE out of the total number asked for consent based on the PAR-Q screener.

#### Implementation Fidelity

Descriptive statistics will be used to calculate the percentage of days that participants wear the study-issued activity tracker, the percentage of participants who participate in the optional PA video chat support meetings, the percentage of videos viewed by participants, and the percentage of days that daily step goals are achieved.

#### Intervention Uptake

Thematic qualitative analysis [57] will be applied to participant exit interview data to identify barriers and facilitators to participants’ uptake of PACE intervention components.

#### Intervention Effects and Maintenance

Activity tracker data will be used to calculate average steps per week. To explore the intervention effects on outcomes (ie, average weekly steps) from baseline to 3 and 9 months after baseline (6 months after intervention), an intent-to-treat analysis scheme will be adopted, and a mixed-effects model will be fitted to estimate the intervention effect on each outcome. Fixed effects terms will include time point (categorical), intervention group, and intervention × time point, and the model will control for the baseline level of the outcome in addition to age and time since diagnosis. A random intercept will be included to account for within-participant correlation. The estimates and tests of the interaction term will be used to assess the preliminary efficacy of the intervention at each time point. Subgroup analysis by sex will be conducted to explore the difference. Missing data will be carefully imputed using mean or median imputation for continuous variables and mode imputation for categorical variables.

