### Data Collection

All outcomes will be measured at baseline, immediately after the intervention (3 months after baseline), and 6 months after the intervention (9 months after baseline). For each assessment point, survey links will be sent via email and SMS text messaging; up to 4 reminders to complete surveys will be sent. Participants may begin the surveys and return to complete them later using a link provided by email upon request. Participants will be sent blood self-collection kits and a prepaid return package at each time point. The collection materials will be labeled with a biosample identifier number unique from their study identifier. The return package will be preaddressed and will contain the return address of the PACE research study to protect against the risk of samples being misplaced or participants being identified during the mailing process. No identifying information beyond the blood samples will be included in the blood return package. If the research team does not receive blood kit return packages within 2 weeks of being mailed, study staff will call and email participants for a maximum of 3 attempts to support participants in completing blood sample collections. If a participant’s daily step count is <200 for 4 consecutive days, an automated email will remind them to wear their activity tracker. Study staff will contact participants via telephone and email for a maximum of 3 attempts to troubleshoot their activity tracker use. Participants in the intervention arm will complete a 15-minute telephone interview after the intervention that includes three questions: (1) What aspects of the PACE intervention did you find most beneficial? (2) Were there any challenges or difficulties you faced while participating in the intervention? (3) Do you have any suggestions for improving the PACE intervention?

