### Limitations and Strengths

Limitations noted in the design of the PACE intervention include the use of self-report measures and the potential for social desirability bias. In addition, depending on how long it takes to obtain consent for participation and set up the activity tracker, participants may begin the PACE intervention at different times after receiving their cancer diagnosis. This may lead to variation in the nature and intensity of side effects participants experience and how effects impact their activity levels. However, the use of a control group, as well as daily step goals that are adaptive to individual participants’ activity levels, will minimize this study’s limitation and allow for the enrollment of participants earlier in the treatment trajectory, as well as an inclusion of a broader range of CRC diagnoses (ie, from early-stage participants undergoing surgery only to those with metastatic disease receiving palliative treatments), all of whom can benefit from PA substantially. Finally, although this study uses previously validated measures, the validity testing for these measures has often been conducted outside the United States, where race and ethnicity are often not reported in study demographics, and much of the research has been conducted with primarily White participants. The PACE study focuses solely on developing and testing an intervention for Black patients because of their historical underrepresentation in prior research. Our study will provide much-needed information on the feasibility of intervention methods and explore intervention effects for this population, including pilot validity data for the exploratory measures used. A further strength of the PACE design is the collaboration with Black survivors of cancer and caregivers in all aspects of this research, from formative research to method development and active engagement in creating and delivering the PACE intervention. Finally, through the use of BCT coding, findings will identify which components of the PACE intervention are most effective and may inform a broad range of future PA interventions for individuals diagnosed with cancer.

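### A random intercept with a single baseline term gives the 3-month and 9-month group contrasts the same standard error, which may be wrong at both visits in an exploratory analysis

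*Protocol article*

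**What the plan says.** The model is set out in the protocol article under Intervention Effects and Maintenance. It lists the main terms first: "Fixed effects terms will include time point (categorical), intervention group, and intervention × time point". On covariate adjustment, the section says that "the model will control for the baseline level of the outcome in addition to age and time since diagnosis". The within-participant structure is given in one sentence: "A random intercept will be included to account for within-participant correlation". The section mentions no visit-specific variance, no other residual structure, no baseline × time point term and no robust standard error. Results are read visit by visit: "The estimates and tests of the interaction term will be used to assess the preliminary efficacy of the intervention at each time point".

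The Data Collection section puts assessments at baseline, 3 months and 9 months, so the gaps are 3 and 6 months. The Feasibility section assigns the post-intervention effects to effectiveness and the effects 6 months after the intervention to maintenance.

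Under PA Measures the article says that the pilot is not powered for statistical significance. It nevertheless makes a power statement for the 9-month visit, with an effect size of d = 0.74: "With 30 participants per group, we will have 80% power to detect a standardized mean difference of" that value.

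**The concern.** A random intercept with independent, constant-variance residuals implies one residual variance for all visits. A single baseline term implies one slope on baseline for both follow-up visits. If baseline predicts the 9-month outcome less well than the 3-month outcome, more unexplained variance is left at 9 months. The model averages the two visits and attaches the same standard error to both group contrasts.

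The maintenance interval (9 months) would then be too narrow and the effectiveness interval (3 months) too wide. With complete data the estimated differences are not biased by this; only their stated precision is wrong. That precision matters because the article intends its results to inform later efficacy work.

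**Working it through.** **The plan's own figure.** With 30 per arm, d = 0.74 and two-sided alpha 0.05 (assumed, since alpha is not stated), the noncentrality is 0.74 × √(30/2) = 2.866 on 58 degrees of freedom. Power from the noncentral t is 80.5%, and the minimum detectable d at 80% is 0.736. The stated 80% reproduces. It is a two-group comparison at one visit and does not use the mixed model.

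**Inputs for the check.** From the article: 30 analysed per arm, visits at 0, 3 and 9 months, random intercept only, one baseline term. Assumed: the correlations and the SD ratio between visits. Age and time since diagnosis are left out, and data are complete.

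**Baseline as a covariate (two modelled visits).** Let the 9-month SD be 1, the 3-month SD k, and a = k·ρ(0–3) and c = ρ(0–9) the covariances with a unit-variance baseline.

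- Common slope: s = (a + c)/2
- True residual variances: v3 = k² + s² − 2sa and v9 = 1 + s² − 2sc
- Variance used by the model at both visits: m = (v3 + v9)/2
- Model SE / true SE: √(m/v3) at 3 months and √(m/v9) at 9 months
- Approximate type I error: 2[1 − Φ(1.96 × ratio)]

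Worked case, k = 1, correlations 0.70 and 0.40: s = 0.55; v3 = 1 + 0.3025 − 0.77 = 0.5325; v9 = 1 + 0.3025 − 0.44 = 0.8625; m = 0.6975. The ratios are 1.144 and 0.899.

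| ρ(0–3), ρ(0–9) | k | SE ratio 3 mo | SE ratio 9 mo | Type I 3 mo | Type I 9 mo |
|---|---|---|---|---|---|
| 0.65, 0.50 | 1.0 | 1.071 | 0.941 | 3.6% | 6.5% |
| 0.70, 0.40 | 1.0 | 1.144 | 0.899 | 2.5% | 7.8% |
| 0.80, 0.51 | 1.0 | 1.224 | 0.866 | 1.6% | 8.9% |
| 0.65, 0.50 | 1.2 | 0.976 | 1.026 | 5.6% | 4.4% |
| 0.70, 0.40 | 1.2 | 1.033 | 0.970 | 4.3% | 5.7% |
| 0.80, 0.51 | 1.2 | 1.093 | 0.927 | 3.2% | 6.9% |

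Simulation agrees. With equal SDs, 40,000 trials per scenario gave 6.3%, 7.3% and 8.4% at 9 months and 3.5%, 2.4% and 1.7% at 3 months. A separate simulation gave 6.8% to 8.9% and 1.7% to 3.4%. With equal correlations and equal variances the rate is about 5% at both visits. Visit-specific variances with visit-specific baseline slopes held 4.8% to 5.1% throughout.

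Under this reading the interaction coefficient is the difference between the 3-month and 9-month group effects. Its standard error comes from the within-participant differences and is correct: simulated rejection was 4.7% to 5.2%.

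**Baseline as an outcome row (three modelled visits).** The interaction terms are now differences in change from baseline, and the equal-correlation constraint binds. With equal SDs and mean correlation r̄, the SE ratios are √[(1 − r̄)/(1 − ρ(0–3))] and √[(1 − r̄)/(1 − ρ(0–9))]. For 0.70/0.60/0.40, r̄ = 0.567 and the ratios are √(0.433/0.30) = 1.20 and √(0.433/0.60) = 0.85. Simulated 9-month type I error over the three correlation sets was 7.4% to 9.6%.

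**The case against.** **No evidence that correlation fades.** The article reports no correlations or visit-specific SDs. A reader might take the Limitations and Strengths section as evidence, because it says "This may lead to variation in the nature and intensity of side effects participants experience". That sentence concerns participants starting at different times after diagnosis, which is a difference between participants, and the model already adjusts for time since diagnosis. It does not say that an individual's measurements become less correlated. Only the unequal visit gaps point that way. This objection stands, and it is why the size is given as an assumed range.

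**The direction is not fixed.** A larger spread at 3 months is plausible, since that is the end of active intervention. A 3-month SD 20% larger brings the two milder cases close to 5% or just past it, although the steepest case still shows about 7% at 9 months. The planned mean imputation, if more data are missing at 9 months, offsets a further part. This also stands.

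**Equal correlation at all visits.** A reader might say that the model forces this. It does so only if baseline is also an outcome row. With baseline only as a covariate there is a single correlation, and the fault is the common residual variance and common slope. It then affects the visit-specific group contrasts and not the interaction coefficient.

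**The 9-month power statement.** A reader might infer that it fails too. It does not depend on this model.

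**Left to the analysis plan, and of small consequence.** Residual structure may be refined in a plan not shown, and no decision rule hangs on these p-values. Both are fair. Even so, the random intercept and single baseline term are stated choices, and the separate 3-month and 9-month effects are what the article sets out to assess.

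**Conclusion.** The point holds in a limited form. As written, the model cannot give the 3-month and 9-month contrasts different precision. If correlation with baseline is weaker at 9 months and the SDs are similar, the 9-month standard error is about 6% to 13% too small and the 3-month one about 7% to 22% too large over the assumed correlations with baseline as a covariate. The range includes no error at all when correlations and variances are equal, and a small reversal when the 3-month spread is larger. The primary outcome is feasibility and the efficacy analysis is described as exploratory, so this is a cheap improvement to a secondary analysis and does not threaten the trial's main conclusion.

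**What to change.** In Intervention Effects and Maintenance:

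- Replace the random intercept with an unstructured residual covariance across visits within participant.
- State whether baseline is a covariate or an outcome row. When it is a covariate, add a baseline × time point term.
- Use Kenward-Roger or Satterthwaite degrees of freedom.
- Report the group difference with its confidence interval at 3 and at 9 months.
- If the model does not converge, use a simpler structure that keeps visit-specific variances, or a separate ANCOVA at each visit.

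The simulations tested visit-specific ANCOVA. With complete data the unstructured model should agree with it closely, but that model with Kenward-Roger degrees of freedom was not itself simulated.

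The cost is one or two sentences, a few more covariance parameters (three in all with two follow-up rows, six with three rows, against two for the random-intercept model) and a small loss of degrees of freedom with about 60 participants. With 16 of 72 participants enrolled at the last count in the article, the change can be made well before analysis.

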## Methods

### Study Design

The PACE feasibility study is a community-based 9-month 2-arm parallel group randomized controlled trial. A total of 72 participants will be enrolled and randomized 1:1 to either an intervention group or a control group. All participants will receive a wearable activity tracker (Fitbit Inspire, Fitbit, Inc) and the American College of Sports Medicine’s “Moving Through Cancer” materials [11]; intervention arm participants will receive the 12-week PACE intervention. Participants will complete study measures at baseline, immediately after the intervention (3 months after baseline), and 6 months after the intervention. Participation will be discontinued if a participant dies or requests to withdraw from the study. Figure 1 shows an overview of the study flow.

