### Outcome Measures

#### Feasibility

The primary study outcome, feasibility, will be determined using the RE-AIM framework [11], with each of the 5 key RE-AIM elements assessed independently and through specific criteria. Rather than a simple “yes or no” determination or a composite score, feasibility will be evaluated based on thresholds for each element. Specifically, reach will be tested by measuring the number of participants contacted, found eligible, recruited, and retained for the duration of the study. On the basis of enrollment in other similar studies [16,23] involving Black participants and patients with CRC, we determined that feasibility would be achieved if 72 participants are enrolled within 18 months and the total attrition rate is <20%. Intervention effectiveness will be tested by measuring intervention effects on selected behavioral, psychosocial, and health-related outcomes, as well as inflammation biomarkers, as detailed subsequently. We anticipated that, compared to the control group, the intervention group will have higher scores on behavioral, psychosocial, and health-related outcomes, as well as on anti-inflammatory biomarkers, and lower scores on proinflammatory biomarkers. Adoption will be measured as the percentage of providers who agree or grant consent for their patients to participate. Implementation fidelity will be assessed as the extent to which the intervention is delivered as intended. This will be measured by the percentage of intervention days that participants wear their Fitbits, the percentage of eligible intervention arm participants attending support sessions, and the percentage of videos viewed relative to the total number of available videos across all participants. While limited published guidance exists on a priori feasibility thresholds [24,25], we have set the feasibility threshold at 60%. This decision is based on recommendations for pilot studies, which suggest selecting a threshold that allows identifying areas where adaptations and improvements can be made in a subsequent efficacy trial [26]. Intervention uptake will be assessed through participant interviews. Intervention arm participants will complete a 15-minute interview via Zoom after the intervention. Using a semistructured format, participants will be asked about their experiences participating in the PACE intervention. Maintenance will be assessed by measuring intervention effects on selected behavioral, psychosocial, health-related outcomes, and inflammation biomarkers 6 months after the intervention. We anticipated that compared to the control group, the intervention group will have higher scores on behavioral, psychosocial, and health-related outcomes, as well as on anti-inflammatory biomarkers, and lower scores on proinflammatory biomarkers.

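### Filling missing outcomes with a mean, median or mode makes the confidence intervals too narrow or shrinks the effect toward zero

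*Protocol article*

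**What the plan says.** Under Intervention Effects and Maintenance, the protocol article states that "an intent-to-treat analysis scheme will be adopted, and a mixed-effects model will be fitted to estimate the intervention effect on each outcome". The fixed effects are time point, group and their interaction, adjusted for the baseline value of the outcome, age and time since diagnosis. "A random intercept will be included to account for within-participant correlation". Inference rests on the interaction: "The estimates and tests of the interaction term will be used to assess the preliminary efficacy of the intervention at each time point".

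The paragraph ends with the missing-data rule: "Missing data will be carefully imputed using mean or median imputation for continuous variables and mode imputation for categorical variables". It does not separate outcomes from covariates, does not say whether the mean is taken over all participants or within arm, and allows for no imputation uncertainty.

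Two other places bear on how much will be missing, and why:

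- The sample size text under PA Measures says: "conservatively, we anticipate 17% total attrition". The Feasibility section sets its attrition limit at below 20%.
- Study Design says: "Participation will be discontinued if a participant dies or requests to withdraw from the study". Limitations and Strengths confirms that the trial is open to "those with metastatic disease receiving palliative treatments".

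**The concern.** A likelihood-based mixed model does not need complete follow-up. Under missing at random it uses each participant's observed values, including a 3-month value when the 9-month value is absent. Filling the gaps first discards that advantage in three ways: the constant is counted as an observation, it ignores the participant's own baseline and 3-month values, and it carries no uncertainty.

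The damage takes one of two forms:

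- **Arm mean:** the filled values add sample size and no spread, so standard errors are too small.
- **Overall mean:** both arms receive the same value, so they are pulled together and the effect shrinks.

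Because the rule has no exception, it would also give average step counts and symptom scores to participants who have died.

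The affected results are the modelled effects at 3 and 9 months, which supply the effectiveness and maintenance elements of the RE-AIM evaluation. The Objectives section says the findings will inform later efficacy work, so a distorted effect or interval would carry over into the planning of the next trial.

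**Working it through.** **Inputs from the protocol article:** 72 randomised 1:1; 17% attrition, leaving 60; 80% power for d = 0.74 at 9 months; attrition limit below 20%; random-intercept model adjusted for baseline.

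**Assumptions (not in the article):** two-sided alpha 0.05; outcome SD 1; correlation 0.5 between any two visits (0.7 as a check); the same effect at 3 and 9 months; half of those missing at 9 months already missing at 3 months; age and time since diagnosis left out; intervals use 1.96.

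**Step 1. The plan's own figure.**
- Attrition: 12/72 = 16.7%, leaving 60.
- Power by the normal approximation: 0.74 × √(30/2) = 2.866, and Φ(2.866 − 1.96) = 0.818. The two-sample t-test gives 0.805. The stated 80% is reproduced.

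**Step 2. What the algebra predicts.** Let m be the fraction missing, equal in both arms.
- *Overall mean.* Each filled arm mean is (1 − m) × observed arm mean + m × overall mean. The difference is therefore (1 − m) × d. With 12/72 missing: 0.74 × 60/72 = 0.617. With 14/72 missing (19.4%, the most that stays under 20%): 0.74 × 58/72 = 0.596.
- *Arm mean.* For one time point without covariates, the apparent variance falls by about (1 − m), and the divisor is n when only n(1 − m) values were observed. The reported SE divided by the correct SE is then about 1 − m = 0.833 with 12/72 missing.

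**Step 3. Simulation of the mixed model.** REML random-intercept fits to the 3- and 9-month outcomes with time, arm × time and baseline; 36 per arm; missing completely at random; 2,000 trials per scenario; no failed fits. The table gives the 9-month effect. Type I error comes from runs with d = 0, the other columns from runs with d = 0.74.

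| Missing | Handling | Mean estimate | True SD of estimate | Model SE | 95% CI coverage | Type I error |
|---|---|---|---|---|---|---|
| 12/72 | none | 0.749 | 0.222 | 0.223 | 95.1% | 5.0% |
| 12/72 | arm mean | 0.750 | 0.229 | 0.195 | 90.5% | 9.5% |
| 12/72 | overall mean | 0.623 | 0.190 | 0.197 | 91.1% | 3.7% |
| 14/72 | none | 0.749 | 0.224 | 0.227 | 95.4% | 4.6% |
| 14/72 | arm mean | 0.749 | 0.233 | 0.193 | 89.1% | 10.8% |
| 14/72 | overall mean | 0.602 | 0.187 | 0.196 | 89.3% | 3.6% |

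The simulation agrees with Step 2. For the arm mean, 0.195/0.229 = 0.85, and 2 × [1 − Φ(1.96 × 0.85)] is about 9.6%, against 9.5% simulated. For the overall mean, 0.623 and 0.602 compare with 0.617 and 0.596. Monte Carlo error on a 5% rate is √(0.05 × 0.95/2000), about 0.5 percentage points.

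**Step 4. Sensitivity to the assumptions.**
- *Dropout likelier at low baseline values, 12/72 missing:* arm mean, coverage 91.2% and type I error 8.8%; overall mean, estimate 0.617; no imputation, 0.743 and coverage 95.8%.
- *Correlation 0.7, 12/72 missing:* arm mean, type I error 10.0%; overall mean, estimate 0.622.
- *Correlation 0.7, 30% missing (above the plan's own limit):* arm mean, type I error 16.6%; overall mean, estimate 0.518 and coverage 74.1%; no imputation, coverage 94.3%.
- *Simpler model (baseline-adjusted OLS, correlation 0.5, 12/72 missing, 6,000 trials):* arm mean, SE ratio 0.824 and type I error 10.4%; overall mean, estimate 0.616.

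**The case against.** The best defence is that this is a feasibility pilot. The article says it is not powered for significance, and the efficacy models are exploratory. Reach, adoption and fidelity are descriptive, uptake is qualitative, and none of the numerical feasibility limits passes through the imputation. That is correct and limits the consequence: no feasibility threshold changes. But effectiveness and maintenance are named elements of the primary evaluation, the plan relies on both estimates and tests for them, and an effect size with an honest interval is what a later trial needs from a pilot.

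A second defence is that the sentence speaks of missing data in general and may be meant for covariates or questionnaire items. Mode imputation does fit poorly with outcomes that are mostly continuous. If only covariates were meant, the harm would be much smaller. Yet the sentence closes the outcome-analysis paragraph without restriction, and randomisation follows confirmed completion of the baseline surveys, so most missing values should be follow-up outcomes. Applying the rule to outcomes is the plain reading.

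Third, the two harms are alternatives. Arm-mean filling left the estimate unbiased when data were missing completely at random. Overall-mean filling did not inflate type I error, and its coverage loss comes from bias. Both points stand, but neither choice gives a sound result.

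Finally, deaths were not simulated and the article gives no death rate. The point about death follows only from the rule having no exception. Median and mode filling were not simulated either.

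**Conclusion.** The concern holds: the rule is wrong as written. This is not a detail left to an analysis plan, because the article names a specific method and that method is unsound for outcomes.

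At the attrition the plan expects, arm-mean filling roughly doubles the nominal 5% error rate (9.5%) and reduces 95% coverage to about 90%. Overall-mean filling removes about one sixth of the effect, because the loss equals the fraction missing (12/72). Both get worse as attrition rises. The planned type of model without imputation performs correctly in the same scenarios.

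The exact sizes rest on the assumed correlation and dropout pattern. The direction does not: it follows from the algebra and persisted with a higher correlation and with dropout dependent on baseline. The conclusion also rests on reading the rule as covering outcomes.

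**What to change.** Replace the imputation sentence with wording to this effect: the mixed model is fitted by REML to all observed 3- and 9-month outcomes, without imputing outcomes, under a missing-at-random assumption; no value is imputed after death, and deaths are reported by arm. Simple mean imputation may stay for an occasional missing baseline covariate.

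A sensitivity analysis for departures from missing at random, by multiple imputation or delta adjustment, is advisable and can be set out in the analysis plan.

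The core change is a sentence or two, with no new data and no change in sample size. With 12/72 missing, the model SE goes from 0.195 under arm-mean filling to 0.223, so the interval is about 14% wider (0.223/0.195 = 1.14) but has its nominal coverage. The sensitivity analysis adds modest analysis work. The Results section reports 16 participants enrolled by June 26, 2025, out of 72 planned, so on that count the change can be made before most outcome data exist.
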